# Comparison of Structural Diagnosis and Management Approach Versus Myofascial Release for Plantar Heel Pain in People With Diabetes Mellitus: A Multicenter Randomized Clinical Trial Protocol

**DOI:** 10.1002/hsr2.72255

**Published:** 2026-04-02

**Keywords:** diabetes mellitus, myofascial release, plantar heel pain, structural diagnosis management

## Abstract

**Background and Aims:**

Plantar heel pain (PHP) is prevalent among individuals with diabetes mellitus and contributes to chronic pain, reduced mobility, muscle weakness, and activity limitation. Conventional treatments such as medications and physical modalities are used but often lack long‐term effectiveness and cost‐efficiency. Physiotherapy approaches, including Structural Diagnosis and Management (SDM) and Myofascial Release (MFR), have demonstrated benefits; however, comparative evidence in diabetic populations is limited. This study aimed to evaluate and compare the effectiveness of SDM and MFR in reducing pain and disability and improving function in people with diabetes mellitus experiencing PHP.

**Methods:**

This study was a multicenter, assessor‐ and participant‐blinded randomized clinical trial. A total of 90 participants with diabetes mellitus, aged 30–65 years, and diagnosed with PHP were recruited from 3 diabetic hospitals in Bangladesh. Participants were randomly allocated (1:1) to the SDM group or the MFR group. Intervention was delivered over 8 weeks, comprising 24 sessions of 45–60 min each. The primary outcome, pain intensity, assessing by Visual Analog Scale (VAS). Secondary outcomes include ankle range of motion, muscle strength, and the Foot Function Index (FFI). The study adhered to CONSORT guidelines, and data analyze in SPSS using the intention‐to‐treat principle.

**Results:**

All primary and secondary outcomes were planned to assess at baseline, postintervention (8 weeks), and follow‐up (20 weeks) to examine both immediate and sustained effects of the interventions, with comparative analyses evaluating the effectiveness of SDM versus MFR in individuals with diabetes mellitus and PHP.

**Conclusions:**

This trial will provide the first direct comparison of SDM and MFR for the management of PHP in individuals with diabetes mellitus. The findings are expected to support evidence‐based, cost‐effective, nonpharmacological physiotherapy interventions and may inform future research and rehabilitation policies in diabetic foot care.

**Trial Registration:**

CTRI/2024/11/076311.

## Introduction

1

Plantar heel pain (PHP) is the most common foot condition affecting the plantar region of the foot and is associated with surrounding structures, including the calf muscle, associated nerves, and plantar fascia, in individuals with a sedentary lifestyle or those who are active and maintain a prolonged standing or walking posture. Clinically, PHP can be associated with plantar fasciitis, typically characterized by discomfort, intermittent pain, and tenderness in the area of fascia located underneath the heel, extending toward the medial longitudinal arch (MLA) of the foot. There are two common clinical conditions associated with PHP, where plantar fasciitis is the most prevalent cause of PHP [1]. The thick band of connective tissue called plantar fascia, which consists of central, medial, and lateral bands. Where the central band arises from the medial tubercle of calcaneal bone toward toes, which provides support for the foot arch, that tissue becomes irritated and inflamed due to tensile overload or force.

Calcaneal spur is another cause. It is a fibromatosis that progressively infiltrates the plantar aponeurosis due to mechanical stress on the foot, gradually and continually increasing in the insertion point [2]. A heel spur is radiologically evident, and pain eventually extends from the heel to the lower extremities, worsening with walking or during the first minutes of rest. Painful ambulation leads to functional impairments. Moreover, this recurrent chronic condition hinders quality of life for an individual and presents with noteworthy disability [3].

The study of PHP incidence and prevalence is limited. It is estimated that 10% of individuals with lower limb pain can experience this condition in their lifespan [4, 5]. An epidemiological study in the United States has demonstrated that nearly one million individuals visit physicians annually for PHP [6]. Risk factors of PHP include obesity, decrease the arches, reduce flexibility, pes planus, improper footwear or hard surfaces of footwear, leading sedentary lifestyle, and prolong working posture in walking or standing barefoot on the hard surfaces or floors [7]. Strong association has been noted with PHP and metabolic diseases such as diabetes mellitus (DM), hyperuricemia, and hyperglycemia. The prevalence of PHP is higher among people with DM and diabetic foot (DF) [8, 9].

Systematic review between (1994 and 2013) reports, 4.5%–35.0% of Bangladeshi people have DM. The number might rise to 13.7 million by 2045 [10]. Approximately one million individuals with DM visit physicians for PHP [11]. Globally, 0.85% of diabetic people have PHP; among them, 1.31% have type‐2 and 0.92% have type‐1 DM [12]. The clinical presentation and biomechanical factors of PHP are similar in both nondiabetic and diabetic patients. However, in DM cases with PHP, elderly women with a high BMI are the most vulnerable group. In DM cases, degeneration of the plantar fascia and repetitive micro‐tears cause relapsing inflammation and delayed healing, creating a vicious cycle of injury and pain.

Shortening of the calf muscle leads to a series of biomechanical abnormalities, such as a decrease in the range of motion (ROM) of dorsiflexion and an increase in stress to the perifascial structures. Diagnosis of PHP can be made based on plantar fascia, heel spur, or myofascial abnormalities of the foot, according to the International Statistical Classification of Diseases and Related Health Problems (ICD) category. Clinical features are categorized according to specific diagnosis. Some clinical examination, such as the windlass test, longitudinal arch angle, tarsal tunnel syndrome test, and active and passive dorsiflexion ROM in the ankle joint, supports the diagnosis [13, 14].

Intervention guidelines for PHP in nondiabetic and diabetic patients are reported similarly in the previous clinical practice guidelines. Medications include anti‐inflammatory agents, such as NSAIDs. Many studies reported the significance of steroid injections in PHP in nondiabetic patients and some in diabetic patients to reduce inflammation, improve pain, and functional conditions. However, steroids have a long‐term consequence of tendon and osseous degeneration [13].

In physiotherapy practice, various interventions have been reported, including electrical modalities such as iontophoresis with dexamethasone 0.4% or acetic acid 5%, which give pain relief and improve function within 2–4 weeks. Manual therapy techniques such as nerve mobilization (effective within 1–3 months), soft tissue mobilization, passive neural mobilization, gliding of the ankle joint posteriorly, the subtalar joint laterally, and the first tarsometatarsal joint anterior‐posteriorly, and distraction manipulation of the subtalar joint are also commonly used to reduce pain and restore mobility for people with PHP [13]. Other conservative approaches include taping, orthotic devices, and night splints. Calcaneal taping may provide pain relief temporarily within 7–10 days. Orthotic devices, such as specially designed foot orthoses, reduce pain and improve function over a short‐term period of approximately 3 months. Night splints, available in sock‐type, anterior, or posterior designs, are recommended for individuals with PHP lasting 6 months or more. They are typically worn for 1–3 months [15].

Studies on PHP in nondiabetic patients have revealed that Myofascial Release (MFR) to the calf muscles and plantar fascia is a practical manual therapy technique [16]. Recent studies indicate that the Structural Diagnosis and Management (SDM) approach—targeting calf muscles, plantar fascia, lower limb muscles, and myoneural structures—offers short‐ to intermediate‐term pain relief and improved functional independence in people with PHP. However, PHP is higher in DM cases and has a poor prognosis, and there is a significant research gap addressing effective manual therapy approaches for PHP in people with DM [17, 18, 19, 20, 21].

Therefore, the primary goal of this study is to compare the effectiveness of two manual therapy approaches, SDM and MFR, in treating individuals with PHP who have DM. The objectives are (1) to determine baseline compatibility of both groups in sociodemographic and clinical variables; (2) to measure between‐group and within‐group posttreatment outcomes in pain, ankle ROM, muscle strength, activity limitation, and disability; and (3) to compare the follow‐up outcomes of both groups. After 8 weeks of interventions, the SDM or MFR group is expected to show better improvement in PHP for people with DM.

## Methods

2

### Study Design

2.1

This study was a multicenter, parallel, assessor‐ and participant‐blinded randomized clinical trial with an 8‐week intervention period, conducted at the Nurul Islam Diabetic Centre, Ibn Sina Diabetes Centre, and City Hospital & Diabetic Care, Jashore, Bangladesh, from September 2025 to March 2026. Eligible participants were randomly assigned in a 1:1 ratio to either the SDM or MFR group. This trial has been designed following the Standard Protocol Items: Recommendations for Interventional Trials (SPIRIT) guidelines, which offer a comprehensive framework for developing RCT protocols, as detailed in Table 1. Additionally, the Consolidated Standards of Reporting Trials (CONSORT) statement has been adopted to improve the quality and completeness of RCT reporting, as shown in Figure 1.

**Table 1 hsr272255-tbl-0001:** SPIRIT table.

Timepoint	Enrollment	Allocation		Post‐allocation	
	−*T* _1_	*T* _0_	*T* _1_	*T* _2_	*T* _3_
*Enrollment*					
Eligibility screening	X				
Informed consent		X			
Demographic and clinical assessment			X		
Group allocation		X			
*Intervention*					
SDM Group			X	X	
MFR Group			X	X	
*Assessment*					
Pain intensity			X	X	X
Range of motion			X	X	X
Muscle strength			X	X	X
Foot Function Index			X	X	X

*Note:* −*T*
_1_, prestudy enrolment; *T*
_0_: group allocation; *T*
_1_, baseline before intervention; *T*
_2_, measurement after 8 weeks; *T*
_3_, measurement after 20 weeks.

Abbreviations: MFR, myofascial release; SDM, Structural Diagnosis and Management.

**Figure 1 hsr272255-fig-0001:**
[figure not shown]
CONSORT flow diagram.

### Sample Size Calculation

2.2

The required sample size was calculated using G*Power software version 3.1.9.7 (University of Kiel, Kiel, Germany). Based on an effect size of 0.50, with a significance level (*α*) of 0.05 and statistical power of 0.80, a total of 72 participants were required for the study. To assume a potential 25% dropout rate, the final adjusted sample size was increased to 90 participants, with 45 allocated to each group [3].

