### Data Analysis

2.15

Data analysis will be performed by an independent statistician using SPSS version 22, with anonymized and encrypted data to ensure confidentiality. Prior to analysis, data will be screened for completeness and outliers. The parametricity of the data will be assessed using the Kolmogorov–Smirnov and Shapiro–Wilk tests, supported by evaluation of skewness and kurtosis and visual inspection of data distribution through histograms and normal probability plots. Descriptive statistics, including mean and standard deviation for normally distributed variables, median and interquartile range for non‐normally distributed variables, and frequency and percentage for categorical variables, will be used to summarize continuous and categorical data. Baseline characteristics, including body mass index and duration of diabetes, will be reported to assess group comparability, and exploratory subgroup analyses for high‐risk participants will be considered if clinically relevant patterns are observed. For comparisons across three time points (baseline, postintervention, and follow‐up), repeated‐measures ANOVA will be applied for normally distributed data, with the Friedman test used as the nonparametric alternative. Between‐group and within‐group differences will be analyzed using independent and paired *t*‐tests for parametric data, or Mann–Whitney *U* and Wilcoxon signed‐rank tests for nonparametric data, as appropriate. The laterality of PHP (unilateral or bilateral) will be recorded and incorporated into the analysis to minimize potential confounding effects on ROM and muscle strength outcomes. Effect estimates and mean differences will be reported with 95% confidence intervals alongside *p* values. All statistical tests will be two‐tailed, with statistical significance set at *p* < 0.05, *p* < 0.01, and *p* < 0.001. In addition, baseline, posttest, and follow‐up change scores will be evaluated, and an intention‐to‐treat analysis using the last observation carried forward method will be applied to handle missing data and preserve the validity of the analysis.

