## Discussion

3

The primary aim of this study is to evaluate the effectiveness of the SDM Approach versus MFR in treating PHP in diabetic patients. Previous research indicates that approximately one million individuals are referred annually to a doctor for a definitive diagnosis of plantar fasciitis. A recent cohort study identified the prevalence of plantar fasciitis as 720,000, with an incidence of 0.85% among diabetic patients [8, 9, 10, 11, 12]. Several studies have explored various interventions that could provide interim relief from PHP, plantar fasciitis, and heel spurs, such as considering and providing anti‐inflammatory agents, electrical modalities, and manual therapies like nerve mobilization, often focusing solely on the central pain area rather than the affected structures [14, 15].

However, our study considers the potential scope by including the associated structures, which may be a more critical factor in achieving sustainable outcomes. Without addressing these, diabetic patients are increasingly at risk of this foot condition, which often remains untreatable and misunderstood. To date, no research has directly compared and analyzed yet the effectiveness of SDM versus MFR in treating PHP in people with diabetes mellitus. The long‐term objective of this study is to play a vital role in the management of this global condition.

This study offers several significant benefits. It marks the first attempt in Bangladesh to compare the effectiveness of SDM and MFR in managing PHP among individuals with diabetes mellitus, incorporating a 12‐week follow‐up period. The study highlights the potential contribution of these intervention strategies not only in reducing pain but also in improving functional outcomes that enhance patients' quality of life. By addressing a significant gap in existing research, this study may offer valuable insights for clinical practice and future research in DF management.

However, limitations include the focus on a specific area in Bangladesh, which may restrict the broader applicability of its findings. Additionally, the presence of multiple comorbidities and a limited sample size are notable constraints. Future research should involve a larger and more diverse population, with an extended follow‐up duration. It is also recommended that subsequent studies adopt more rigorous research designs, suited to resource‐limited settings, to enhance the validity and generalizability of the findings.

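### The 72 participants in section 2.2 do not give 80% power for an effect size of 0.50: the planned two-sided t-test between arms needs 128, and 72 give about 55%

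*Protocol article*

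**What the plan says.** Section 2.2 (Sample Size Calculation) of the protocol article reports a G*Power calculation: "Based on an effect size of 0.50, with a significance level" of 0.05 and "statistical power of 0.80, a total of 72 participants were required for the study". The total is then raised to 90 (45 per arm) for 25% dropout. The section names neither the test family nor the effect-size metric (Cohen's d or f), and gives no correlation between repeated measurements.

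Section 2.1 gives two parallel arms, 1:1, measured at baseline, week 8 and week 20. Section 2.9 makes VAS pain the primary outcome.

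Section 2.15 (Data Analysis) says "All statistical tests will be two‐tailed". Between-group and within-group "differences will be analyzed using independent and paired" t-tests, or rank tests where normality fails. Repeated-measures ANOVA is also planned across the three time points, and missing values are carried forward under intention to treat.

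Section 3 (Discussion) concedes that multiple comorbidities and "a limited sample size are notable constraints", but does not revise the power claim.

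**The concern.** The four printed figures (effect 0.50, alpha 0.05, power 0.80, total 72) do not fit together for the between-arm test that the article itself specifies. An effect of 0.50 with a two-sided two-sample t-test is a familiar case, and its answer is well above 72.

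The claim concerns the main design property of the trial. Two active manual therapies are compared on pain, so a non-significant difference is a realistic outcome. A reader who believes the trial had 80% power for a moderate effect would give such a result more weight than it deserves. The article does not itself propose an equivalence reading. The risk lies in what an overstated power figure invites.

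**Working it through.** **Inputs.** Effect 0.50, alpha 0.05, power 0.80, total 72, enrolled 90, dropout 25% (section 2.2); 1:1 allocation (section 2.1); two-sided independent t-test (section 2.15). The effect is read as Cohen's d because the test is a two-sample t-test.

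**Trying to reproduce 72 from the printed inputs**

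| Reading of 0.50 | Test | Total N for 80% |
|---|---|---|
| d | two-sample t, two-sided | 128 |
| d | two-sample t, one-sided | 102 |
| d | Mann-Whitney, two-sided, normal data | about 134 |
| d | paired t, two-sided / one-sided | 34 / 27 |
| f | one-way ANOVA or ANCOVA, two groups | 34 |
| f | repeated measures, 3 visits, correlation 0 to 0.8 | at most 30 |

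None gives 72.

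**The planned test.** With n per arm, degrees of freedom are 2n − 2 and the noncentrality is δ = d√(n/2). Power is the probability that a noncentral t exceeds the two-sided 5% critical value in absolute size.

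- n = 63: δ = 0.5√31.5 = 2.806; power 79.5%.
- n = 64: δ = 0.5√32 = 2.828; power 80.1%. So 64 per arm, 128 in total.

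**Power for d = 0.50 at the trial's own sizes**

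| Analysed | n per arm | δ | Two-sided power | d detectable with 80% power |
|---|---|---|---|---|
| 90 × 0.75 = 67.5 | 33.75 | 2.054 | 52.5% | about 0.69 |
| 72 | 36 | 2.121 | 55.3% | 0.67 |
| 90 | 45 | 2.372 | 65.0% | 0.60 |

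Even one-sided, which section 2.15 rules out, the power is 67.6% with 72 and 76.1% with 90.

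**The one route that lands near 72.** Convert d = 0.50 to f = 0.25 and use the between-groups test of a repeated-measures ANOVA with m measurements and correlation ρ: λ = N f² m / (1 + (m − 1)ρ), on 1 and N − 2 degrees of freedom. With m = 3:

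- ρ = 0.33, N = 72: λ = 72 × 0.0625 × 3 / 1.66 = 8.13; power 80.3%.
- Smallest equal-arm N: 70 at ρ = 0.3, 78 at 0.4, 86 at 0.5.

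With m = 2, a correlation of about 0.1 also leads to 72. The result depends heavily on a correlation that is not stated.

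This test uses the arm difference averaged over all visits. If the arms differ by 0.50 at weeks 8 and 20 and by nothing at baseline, as randomisation leads one to expect, the averaged difference is two thirds of 0.50. Then f = 0.25 × 2/3 = 0.167, λ = 72 × 0.0278 × 3 / 1.66 = 3.61, and power at 72 falls to about 47%.

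**Baseline-adjusted analysis (not planned).** ANCOVA with baseline-outcome correlation r replaces d by d/√(1 − r²). With 90 analysed and d = 0.50:

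- r = 0.5: 0.5/√0.75 = 0.577; power 77%.
- r = 0.6: 0.5/√0.64 = 0.625; power 83%.

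At 72 it needs r of roughly 0.66 to 0.7 to reach 80%.

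**The case against.** The strongest objection is that section 2.2 never says which G*Power test was run, so the t-test basis is taken from section 2.15. That section also plans repeated-measures ANOVA over three visits, and f = 0.25 with a correlation of 0.33 gives 72. The figure may be a genuine program output whose settings the article left out, and a condensed article may leave settings to a fuller document. This stands as a possible explanation of where 72 came from. It does not rescue the claim: the conversion, the test family and the correlation appear nowhere, and that test averages in a baseline visit at which randomised arms should not differ. It does not power the comparison of interest.

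A second objection is that the planned analysis carries values forward under intention to treat, so all 90 would be analysed. The relevant power would then be 65%, not 55%. This is fair, and the chance of missing a true 0.50 is then about 35% instead of 45%. But 55% is the right figure for the 72 that section 2.2 calls sufficient, and 65% is likely to be optimistic if there are dropouts, because carried-forward values may dilute the difference.

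Third, the Discussion already admits a limited sample. It does so in general terms and leaves the 80% in place.

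**Conclusion.** The power statement in section 2.2 is wrong as written. For the two-sided independent t-test in section 2.15 and a standardised difference of 0.50, 128 participants are needed where 72 are claimed, a shortfall of 128 − 72 = 56. Power is 55% at 72, 65% at 90 and about 53% after 25% loss, so no enrolment scenario within the plan reaches 80%.

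These figures assume that 0.50 is Cohen's d, that the outcome is roughly normal with equal variance in the arms, and that the primary comparison is unadjusted. What is certain is that 72 does not follow from the printed inputs under any standard reading. Which calculation produced it cannot be determined from the article.

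**What to change.** Keep the enrolment of 90 and correct section 2.2:

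- Name the test, the sidedness, the effect-size metric and the outcome and time point it refers to.
- State that, with an unadjusted two-sided t-test on VAS, 72 analysed give 80% power for d of about 0.67 and 55% for d = 0.50. With 90 analysed the corresponding figures are 0.60 and 65%.
- If a repeated-measures calculation was in fact used, give its f, number of measurements and correlation, and say that its contrast includes baseline.
- If the primary analysis is changed to baseline-adjusted ANCOVA before the data are unblinded, restate the power with the assumed correlation shown: for d = 0.50 and 90 analysed, 77% at r = 0.5 and 83% at r = 0.6. The article gives no value for r, so it must be labelled as an assumption.
- Add that a non-significant difference will not be read as similarity of the two treatments, and that the confidence interval will carry the interpretation.

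The cost is one rewritten paragraph and a less favourable power statement. No additional participants are required.

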### Randomization and Blinding

2.5

Eligible participants with written informed consent were randomly allocated to their respective groups, either the SDM or the MFR group. The randomization sequencing process was conducted using the “Rand” function in Microsoft Excel 2013 software. A sequential list of participants' IDs, sorted according to the randomly generated numbers. This procedure helps to prevent bias. Participants were allocated to a parallel intervention group in a 1:1 ratio. This is an assessor‐ and participant‐blinded randomized clinical trial, with outcome assessors and participants blinded to group allocation. Physiotherapists delivering manual therapy could not be blinded, but both groups received identical conventional physiotherapy to control for nonspecific effects. Therapists were trained to follow standardized protocols and avoid discussing treatment or outcomes with participants or assessors to minimize bias. Inter‐rater reliability for manual techniques will be established, and any unblinding will be documented and reported.

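### Ninety randomised participants cover 20% dropout, not the stated 25%: a quarter lost from 90 leaves about 67, below the required 72

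*Protocol article*

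**What the plan says.** Section 2.2 of the protocol article reports a G*Power calculation with the inputs "Based on an effect size of 0.50" and a significance level "of 0.05 and statistical power of 0.80". Its result is that "a total of 72 participants were required for the study". The dropout allowance follows in the next sentence: "To assume a potential 25% dropout rate, the final adjusted sample size was increased to 90 participants", which is 45 per group. The inflation formula is not written out and no other allowance is described. The abstract repeats the total of 90, and section 2.5 (Randomization and Blinding) confirms equal allocation. Section 2.15 (Data Analysis) makes all tests two-tailed and plans an intention-to-treat analysis with last observation carried forward for missing data.

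**The concern.** An allowance for dropout is meant to leave the required number of participants with outcome data after the expected losses. The three figures in section 2.2 (72 required, 25% lost, 90 randomised) cannot all hold in that sense. The total looks like the common slip of adding 25% of the requirement, when the requirement should be divided by the fraction expected to remain.

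A reader of section 2.2 will conclude that the calculated requirement survives 25% attrition. If it does not, the trial has no margin at the very dropout rate it planned for, and the final assessment is not until week 20, 12 weeks after treatment ends.

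**Working it through.** **Inputs, from section 2.2 unless noted**

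- Required number before dropout: 72 in total
- Dropout rate: 25%
- Final number: 90, 45 per group
- Allocation 1:1 (section 2.5) and two-sided tests (section 2.15), used only for the power figures

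**Step 1. Reproduce the plan's figure.** N × (1 + d) = 72 × 1.25 = 90, an exact match. The formula is inferred, since the article does not give it.

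**Step 2. How many remain at the stated dropout?** 90 × (1 − 0.25) = 67.5, so about 67. The shortfall is 72 − 67.5 = 4.5, that is 4 to 5 participants. This follows from the stated figures however the 90 was reached.

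**Step 3. What number preserves 72?** N / (1 − d) = 72 / 0.75 = 96, or 48 per group. Check: 96 × 0.75 = 72. The plan is 96 − 90 = 6 randomised participants short.

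**Step 4. What dropout does 90 cover?** 1 − 72/90 = 0.20, so 20%.

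**Step 5. Effect on power.** The article names neither the effect-size metric nor the test, so two readings are shown. Both assume a two-sided two-sample t-test at 0.05 with equal groups, and power comes from the noncentral t distribution.

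| Reading | 72 with data (36 per group) | 67.5 with data (33.75 per group) |
|---|---|---|
| Stated 80% at 72 taken at face value (implies a standardised difference of about 0.67) | 0.80 | 0.77 |
| 0.50 taken as Cohen's d | 0.553 | 0.525 |

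The loss is about 3 percentage points either way (0.80 − 0.77 = 0.03; 0.553 − 0.525 = 0.028). The low absolute level in the second row comes from the 72 itself, which does not match d = 0.50 under that reading. That is a separate question, and nothing in steps 1 to 4 depends on it.

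**The case against.** The arithmetic is not in dispute; the case on the other side concerns what it means.

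- **The consequence is small.** It amounts to about 3 points of power, and only if dropout reaches the full 25%. At 20% or less, 72 is met. This stands, and it limits the weight of the point.
- **The article never says in so many words that 72 will remain after 25% dropout.** That is correct, but no other purpose is given for raising 72 to 90 on account of dropout, and the article speaks of a dropout rate, not a 25% margin added to 72.
- **The planned analysis carries the last observation forward, so nominally all 90 are analysed and 67 is not the analysis number.** The wording of any correction should respect this: 67 is the number with observed outcomes. The objection does not rescue the calculation. Imputed values do not restore lost follow-up information, and if carrying values forward made dropout harmless, an allowance on 72 would have no purpose.
- **The 53% and 55% figures rest on an unstated effect-size metric and bring in doubts about the 72.** This is fair. They are therefore labelled as an assumption here, and the point is judged on 90 against 96 alone.

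**Conclusion.** The point holds. Taking 72 as given, 90 randomised participants do not preserve it at 25% dropout, and nothing elsewhere in the article repairs this. The true tolerance is 20%. At 25% about 67 would have observed outcomes, 4 to 5 too few, and a consistent total would be 96. This rests only on the three stated figures and on reading a dropout rate as a share of those randomised.

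The consequence is modest: about 3 percentage points of power at 25% dropout, on the t-test assumption in either reading. It is a wrong design figure that should be corrected, but by itself it does not threaten the trial's ability to answer its question.

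**What to change.** Keep 90 and replace the dropout sentence in section 2.2 with wording such as: *Randomising 90 participants (45 per group) leaves 72 with observed outcomes at 20% dropout; at 25% dropout about 67 would have observed outcomes.* Add the power at 67, computed with the test and effect-size metric actually used in G*Power, and name both. Say that these are participants with observed outcomes, so that the sentence agrees with the intention-to-treat analysis in section 2.15.

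The cost is one sentence and a stated tolerance lowered from 25% to 20%, with no extra participants. The article reports that recruitment is still under way, so the correction can be made before results are known. If the sponsor prefers to keep the 25% tolerance, the consistent total is 96 (48 per group), six more participants. If the 72 is itself revised, the allowance should be recomputed from the new figure by dividing by one minus the dropout rate.
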